**1.** **Abstract (200 words)**

Fibromyalgia (FM) is a syndrome characterized by chronic widespread pain, fatigue, and sleep disturbances. Current treatment often relies on pharmacological interventions, whose effectiveness is limited by adverse effects and poor adherence. In contrast, physical exercise has proven beneficial for pain relief and functional improvement. However, persistent pain in FM patients complicates adherence to exercise, necessitating additional complementary strategies. Immersive virtual reality (IVR) has emerged as a promising approach to modulate pain perception through sensory immersion and cognitive distraction. Although IVR has been used in FM through exergames—interactive videogames designed to make physical activity more engaging—its concurrent application with therapeutic exercise remains underexplored. Immersion in virtual environments may positively influence perceived exertion and range of motion, ultimately optimizing the benefits of exercise.

This study aims to evaluate the efficacy of an IVR system that modifies the patient’s visual feedback by creating the illusion of reduced bodily movement during resistance exercises. The hypothesis is that such manipulation may enable greater range of motion without exacerbating pain or perceived effort, thus enhancing the therapeutic outcomes in patients with FM. This innovative approach could pave the way for more effective, patient-centered interventions and promote better adherence to exercise programs.

.

**2. Introduction**

Fibromyalgia (FM) is a condition of unknown etiology, primarily characterized by chronic (>3 months), widespread pain that affects multiple body regions^1^. While the most distinctive clinical feature is widespread pain, FM is a complex, polysymptomatic disease encompassing additional core symptoms, such as fatigue and sleep disturbances^2–4^. Moreover, this condition is commonly accompanied by cognitive dysfunction^3^; regional pain syndromes^5–9^; autonomic alterations^10–16^; psychiatric symptoms^17–19^; and hypersensitivity to external stimuli, as summarized in Figure 1.

[figure not shown]

Prevalence estimates of FM vary considerably depending on the diagnostic criteria used. According to the American College of Rheumatology (ACR) 1990 guidelines, rates range from 0.4% to 8.8%, with a global average estimated at 2.7%. In Europe, a multinational study conducted in France, Portugal, Spain, Germany, and Italy reported a prevalence of 4.7% and a female-to-male ratio of 3:1 ^20^. Recognized as the third most common musculoskeletal disorder—after low back pain and osteoarthritis—its frequency increases with age, peaking between 50 and 60 years of age ^21,22^. However, variations in patient-reported data and insufficient clinical recognition may affect the precision of these estimates ^23^.

The quality of life among individuals with FM is severely compromised by the characteristic symptoms of the disease, as evidenced by the high healthcare costs it incurs. The annual number of medical visits is nearly double that of healthy controls, and total healthcare expenditures are roughly three times higher ^24,25^. Indirect societal costs are also substantial, primarily due to reduced work productivity ^26,27^; one study found that 24.3% of patients were no longer working five years following FM onset ^28^. Furthermore, healthcare expenditures are directly related to FM symptom severity ^29^, underscoring the need for effective and sustainable therapeutic strategies. Although pharmacological treatments can provide symptom relief, they are often associated with a high incidence of adverse effects and lower patient adherence^30^.

By contrast, physical exercise (PE) has become a well-documented, effective therapeutic tool for managing FM. Multiple studies have demonstrated its benefits, including pain reduction, enhanced quality of life, increased physical capacity, and decreased depressive symptoms. Particularly effective modalities include resistance training ^31–36^ and aerobic exercise ^31,32,37–39^, both of which are widely recommended for FM management. Nevertheless, considering the complex and multidimensional nature of chronic pain, additional complementary strategies have been explored.

In this regard, virtual reality (VR) has emerged as an innovative approach with significant therapeutic potential. Recent evidence suggests that VR can modulate pain perception through sensory immersion, cognitive distraction, and multisensory stimulation, making it a promising technique for improving pain control in FM patients ^40,41^. VR technologies are typically classified into three categories based on their immersion level: non-immersive, semi-immersive, and fully immersive. The degree of immersion has a direct impact on the user’s perceptual and psychological experience, as well as their sense of embodiment within the virtual environment ^42^.

In the context of FM treatment, non-immersive VR devices, often in the form of exergames, have been the most frequently employed. Despite offering a limited degree of immersion, these approaches have shown efficacy in improving critical variables in FM populations, including disease impact, pain, dynamic balance, aerobic capacity, fatigue, quality of life, anxiety, and depression ^43–53^. Conversely, immersive virtual reality (IVR) offers a substantially higher level of immersion ^42,54^. This modality not only enhances the user’s sense of embodiment but can also deliver real-time feedback^55^. Studies indicate that higher immersion quality correlates with stronger pain distraction effects, wherein greater immersion leads to more pronounced pain reduction compared to less immersive approaches ^56^.

IVR has thus emerged as an innovative therapeutic tool, not only for modulating pain perception but also for improving functionality in patients with FM ^57–59^. While extensive research has examined IVR in the context of exergames or as an adjunct after exercise, its simultaneous application during therapeutic exercise remains underexplored. Furthermore, the potential benefits of manipulating visual feedback in an IVR environment during a therapeutic exercise program for FM have yet to be thoroughly investigated.

To our knowledge, no existing studies have evaluated the impact of a therapeutic exercise program incorporating IVR with modified visual feedback on FM symptoms. Therefore, the primary goal of the present study is to determine the efficacy of an IVR system that adjusts the patient’s visual perception, creating the illusion of reduced bodily movement compared to actual movement during resistance training. This manipulation may enable an increased range of motion without heightening perceived effort or pain, thereby optimizing overall treatment efficacy.

**3.Objectives**
**Objective 1:** Evaluate the effectiveness of immersive virtual reality combined with resistance exercises in alleviating fibromyalgia-related pain in patients’ daily lives.
**Objective 2:** Determine the capacity of immersive virtual reality combined with resistance exercises to improve the quality of life and functional capacity of patients with fibromyalgia.
**Objective 3:** Examine the effectiveness of immersive virtual reality combined with resistance exercises in bringing about changes in the degree of central sensitization among fibromyalgia patients.

**4. Methodology:**

**4.1 Study Design**
This Randomized Clinical Trial (RCT) is designed to evaluate the efficacy of immersive virtual reality in patients with fibromyalgia. Participants will be randomly assigned to two groups. The intervention group will receive therapeutic exercise combined with immersive virtual reality, while the control group will perform only resistance exercise. The goal is to determine whether immersive virtual reality leads to a significant improvement in outcomes for the intervention group compared to the control group.

**4.2 Target Population and Study Population**
Adults of both sexes, aged 18 or older, diagnosed with fibromyalgia (according to ACR 1990, 2010, 2011 and 2016 criteria).

**4.3 Selection Criteria**
The selection criteria for this study follow the standardized guidelines commonly used in research involving therapeutic exercise and/or immersive virtual reality for patients with fibromyalgia.

Participants will be included if they meet the following requirements: adults of both sexes, over 18 years of age, diagnosed with fibromyalgia based on any of the American College of Rheumatology (ACR) criteria (1990, 2010, 2011 or 2016), able to communicate with the study staff, willing to participate by signing the informed consent form, and reporting a perceived pain score of 3 or higher on a 11-point Numerical Pain Rating Scale (NPRS-11)

Exclusion criteria include the presence of additional conditions and/or symptoms contraindicating immersive virtual reality and exercise, pathologies that could interfere with study outcomes (e.g., visual, auditory, perceptual, or sensory disorders), the use of medication that could affect study results, concurrent therapeutic physical activity treatment during the intervention, or any changes to usual treatments—be they pharmacological or physical therapies—during the intervention.

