**4.4 Sample size calculation**

The primary outcome is FIQR. The between-group MCID is ≈14% of the FIQR total score. Assuming SD=20, α=0.05 and power=80% with ANCOVA adjusted for baseline, 32 per group are required (total 64). Allowing 25% attrition, the target sample size is 80.

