**4.6 Type of Sampling and Randomization**

Participant recruitment and written informed consent will be obtained by physicians from the “Estilo de vida y salud” research group at CEU Cardenal Herrera University. Randomisation will be conducted by an independent researcher using a computer-generated 1:1 sequence with stratified permuted blocks of random sizes (2–4) within eight strata defined by sex (male/female) and FM severity (four FIQR clusters per Pérez-Aranda et al., 2019 [32]). Allocation will be concealed with sequentially numbered, opaque, sealed envelopes (SNOSE) prepared off-site with tamper-evident seals and carbonless copies. After baseline assessment, site staff will open the next envelope in numerical order to assign the experimental group (EG) or control group (CG). The randomisation list will be held by an independent data manager with no role in enrolment or assessment. Any deviation from sequence or envelope integrity will be recorded and investigated. Outcome assessors and the trial statistician will be blinded to group allocation. Participants and intervention providers cannot be blinded due to the nature of immersive VR and will be instructed not to disclose allocation during assessments. Assessments will be performed by personnel without access to scheduling or allocation logs; groups will be labelled A/B until database lock. Unblinding will occur only to address serious safety concerns or protocol deviations with safety implications, following written authorization from the Principal Investigator; all unblinding events will be logged. The allocation list will remain with the independent data manager.

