**4.8 Intervention**

The intervention programme will last a total of six weeks, with two weekly sessions of 60 minutes each. Sessions will take place in AVAFI’s facilities, in a climate-controlled room that meets the necessary space and privacy requirements. Each session will be led by a researcher responsible for ensuring proper exercise execution and participant well-being. The session will be divided into three distinct phases:

- **Warm-Up Phase (5 minutes):**

Joint mobility exercises combined with breathing techniques to prepare the body for physical activity. These exercises will focus on the cervical and lumbopelvic areas and the upper and lower extremities, without additional load.

- **Main Intervention Phase (50 minutes):**

Participants will carry out a therapeutic exercise programme tailored to their group (intervention or control), with intensity regulated through the Borg Scale (6–20). Sessions will be supervised by a researcher to ensure proper exercise execution and participant safety. Exercises are illustrated in Figure 2 and will include trunk flexion, extension, rotation, and side bending in various positions (standing, seated, and lying down). Participants will be instructed to synchronize the concentric and eccentric phases with their breathing to maintain a consistent execution speed.
The programme will focus on exercises using body weight, and starting from the sixth session, ankle weights and some dumbbell exercises will be added. Participants will perform between 1 and 2 sets of each exercise, adjusting intensity and repetitions according to their perceived exertion, assessed using the Borg Scale (6–20), aiming for an intensity range between 13 and 17. During each session, pain intensity (NPRS-11), perceived exertion (RPE), and well-being associated with Virtual Reality will be recorded.

- **Cool-Down Phase (5 minutes):**

Stretching and breathing exercises to reduce muscle tension and promote relaxation. These will include stretches for the lumbar region and lower extremities, along with deep breathing exercises performed in a supine position.

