**4.10 Information on the Proposed Data Analysis**

All analyses will follow the intention-to-treat principle.

Primary outcome (FIQR). Intervention effects will be assessed using a two-way repeated-measures ANCOVA with one within-subject factor (Time: t0, t1) and one between-subject factor (Group: IVR+exercise vs exercise). The dependent variable will be the post-intervention score (t1), adjusted for its baseline value (t0). Sex and baseline FIQR will be included as prespecified covariates. Results will be reported as adjusted mean differences with 95% confidence intervals. Statistical significance will be set at two-sided p<0.05.

Secondary outcomes will be analyzed using the same ANCOVA framework (t1 adjusted for t0), with Group as the between-subject factor and the same covariates (sex and baseline FIQR). Within-group standardized effect sizes (Cohen’s d) will be presented descriptively.

All analyses will be performed in SPSS v27.0 (IBM Corp., Armonk, NY, USA).

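### The exclusion for changes to usual treatment during the intervention can be observed only after randomisation and, applied as written, conflicts with the intention-to-treat statement

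*Protocol*

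**What the plan says.** Section 4.3 (Selection Criteria) opens its list with "Exclusion criteria include the presence of additional conditions and/or symptoms contraindicating immersive virtual reality and exercise" and ends it with "concurrent therapeutic physical activity treatment during the intervention, or any changes to usual treatments". It adds that the changes may be to drugs or to physical therapies and that they are changes made while the intervention runs. No size or type of change is specified.

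Section 4.6 fixes when allocation happens: "After baseline assessment, site staff will open the next envelope in numerical order to assign the experimental group (EG) or control group (CG"). The treatment period comes after that; under Section 4.8, "The intervention programme will last a total of six weeks, with two weekly sessions of 60 minutes each". Section 4.6 also concedes that "Participants and intervention providers cannot be blinded due to the nature of immersive VR".

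Section 4.10 states that "All analyses will follow the intention-to-treat principle". Section 5.5 says that participants are selected by the inclusion and exclusion criteria and that they may withdraw at any time. No section says what happens to a randomised participant whose usual treatment changes.

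**The concern.** An exclusion criterion should rest on facts available before allocation. A change in usual treatment over the following six weeks is not such a fact. If staff treat it as an exclusion, the only person it can exclude is one already randomised, and intention-to-treat calls for that person's data.

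The event is also unlikely to be neutral. In fibromyalgia, a change of analgesic or physiotherapy may well follow poor symptom control, which the self-reported FIQR measures. Participants and providers know the allocation, so the frequency of changes, and of their being reported or acted on, could differ between arms. Removing people on that basis would compare two selected groups. Neither blinded assessors nor adjustment for baseline FIQR repairs this, because the selection happens after baseline. If removal also means no t1 assessment, the data cannot be recovered at the analysis stage.

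**Working it through.** **1. Timing of the two criteria**

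| Criterion (Section 4.3) | Knowable before allocation? | Consequence |
|---|---|---|
| Change to usual treatment during the intervention | No. At most, a planned change can be asked about | As worded, acts only on randomised participants |
| Concurrent therapeutic physical activity during the intervention | Partly. A current or booked programme that will overlap the six weeks can be asked about | Can be read as a screening question; wording needs clarifying |

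Set beside Section 4.10, the first row gives two instructions about the same people: exclude them, and analyse everyone by intention-to-treat.

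**2. The plan's own sample size**

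Inputs from Sections 4.4 and 4.10: "The between-group MCID is ≈14% of the FIQR total score", taken as 14 points on the 0–100 scale; SD 20; two-sided α 0.05; power 80%.

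n per arm = 2 × [20 × (1.960 + 0.842) / 14]² = 32.04. The plan's 32 reproduces (power at 32 per arm 79.96%) without using any baseline correlation.

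**3. Bias if treatment changers are excluded (all rates assumed; the protocol gives none)**

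*Simple form.* Suppose changers score δ points worse at t1 than the others in their arm. Excluding them moves the between-group difference by δ × (difference in exclusion proportions). With 20% of controls and 10% of the virtual-reality arm changing:

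- δ = 10: 10 × (0.20 − 0.10) = 1 point
- δ = 20: 20 × (0.20 − 0.10) = 2 points

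*Latent-variable form, no true effect.* FIQR has SD 20, and the tendency to change treatment correlates 0.5 with a worse score. If a proportion p of an arm is excluded, the mean of those left shifts by −0.5 × 20 × φ(z) / (1 − p), where z is the (1 − p) normal quantile and φ the normal density.

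| p | Shift in arm mean |
|---|---|
| 5% | −10 × 0.1031 / 0.95 = −1.09 |
| 10% | −10 × 0.1755 / 0.90 = −1.95 |
| 15% | −10 × 0.2332 / 0.85 = −2.74 |
| 20% | −10 × 0.2800 / 0.80 = −3.50 |
| 25% | −10 × 0.3178 / 0.75 = −4.24 |

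| Exclusion rates in the two arms | Spurious difference in FIQR points |
|---|---|
| 10% and 10% | 0 |
| 5% and 15% | 2.74 − 1.09 = about 1.7 |
| 10% and 20% | 3.50 − 1.95 = about 1.6 |
| 5% and 25% | 4.24 − 1.09 = about 3.1 |

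The spurious benefit goes to the arm with more exclusions. A simulation with two million draws per scenario gave the same values (1.65, 1.56 and 3.15; zero under equal rates).

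**4. Precision**

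Power = Φ(14 / (20 × √(2/n)) − 1.96), with n per arm. Eighty randomised less 25% leaves 60, or 30 per arm, with power 77.4% before this criterion is applied. Further exclusions, at assumed rates:

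| Further exclusion | n per arm | Power |
|---|---|---|
| 0% | 30 | 77.4% |
| 5% | 28.5 | 75.3% |
| 10% | 27 | 73.0% |
| 20% | 24 | 67.9% |

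These figures ignore any gain from baseline adjustment, as the plan's 32 does.

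**The case against.** The strongest reply is that the conflict is inferred. Section 4.3 is about selection and Section 4.10 about analysis. Read together, the first decides who enters and the second who is analysed. Section 5.5 describes withdrawal only as the participant's own choice. A reader might infer that the protocol orders treatment changers to be withdrawn or left out of the analysis, but no sentence says so. This stands, and the point is limited accordingly: the conflict arises when the criterion is applied as worded.

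A reader might also infer that both criteria are post-randomisation exclusions. The documents do not support that for concurrent activity, because someone already in another programme, or booked into one, can be identified at screening. A planned treatment change can be asked about too, but the criterion covers any change that occurs, planned or not, so its timing problem remains.

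A third reading is that these exclusions come on top of the planned 25% attrition and bring power down to about 70%. Section 4.4 does not define attrition, so the 25% may already cover such losses. Power at 30 per arm is already about 76% (t-test) to 77% (normal approximation), so most of the gap from 80% to 77% or below has another source at low exclusion rates. Baseline adjustment could offset the loss: at 26 per arm, an assumed correlation of 0.3 or 0.5 gives about 74% or 81% by t-test.

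Finally, definitions of analysis sets commonly sit in the statistical analysis plan, and their absence here is no fault. But eligibility belongs in the protocol, and an analysis plan cannot restore t1 assessments that were never made because a site applied an exclusion.

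**Conclusion.** The concern holds for the treatment-change criterion. It can be observed only after allocation, and applying it as written conflicts with the intention-to-treat statement. The concurrent-activity criterion needs clarification only.

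The textual conflict rests on no assumption about rates. The size of any bias does: about 1 to 3 FIQR points when exclusion differs by 10 to 20 percentage points between arms and changers do worse, and zero when exclusion is equal and equally related to outcome. One to 3 points is roughly 7% to 22% of the 14-point target (1/14 = 7%; 3.1/14 = 22%). The direction is unknown, because the protocol gives no ground for saying which arm would see more changes. Any loss of power is conditional on what the 25% allowance covers and is secondary to the question of who enters the primary analysis. The correction should be made before enrolment because t1 data not collected cannot be recovered.

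**What to change.** Reconcile Sections 4.3 and 4.10.

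- **Eligibility (4.3).** Restrict both criteria to facts known before randomisation: a current or planned concurrent therapeutic exercise programme that would overlap the intervention, and a change to usual treatment already planned at enrolment.
- **After randomisation (4.3 or 4.10).** State that participants whose treatment changes, or who start another programme, are still assessed at t1 and included in the primary analysis in the arm to which they were allocated, and that such changes are recorded and reported by arm.
- **Optional.** An analysis without these participants may be added if it is labelled as a sensitivity analysis.

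This concerns eligibility, follow-up and analysis only; it sets no rule on treatment. No stated sample-size figure changes. The cost is rewording the criteria, one or two added sentences, and recording concomitant treatment at t1. The price in interpretation is that the estimated difference then includes the effect of treatment changes made during the six weeks.

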**4.4 Sample size calculation**

The primary outcome is FIQR. The between-group MCID is ≈14% of the FIQR total score. Assuming SD=20, α=0.05 and power=80% with ANCOVA adjusted for baseline, 32 per group are required (total 64). Allowing 25% attrition, the target sample size is 80.

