4.9 Outcomes and measurement instruments

1. The FIQR is a validated, widely used instrument for assessing the impact of fibromyalgia on patients’ daily lives. It evaluates three key dimensions: functionality (9 items, 0–30 points), symptoms (10 items, 0–50 points), and overall impact (2 items, 0–20 points), yielding a total score from 0 to 100. Higher scores reflect a greater impact of the disease. Each item is rated from 0 to 10, indicating no impairment to maximum impairment. The Spanish version of the FIQR has demonstrated high reliability (Cronbach’s α = 0.91–0.95) and is considered the reference instrument for evaluating the effectiveness of fibromyalgia interventions, given its sensitivity to detect change and its strong support in the scientific literature ^61,62^.
2. The EQ-5D-5L is a validated questionnaire translated into Spanish for assessing quality of life. Developed by the EuroQol Group as an enhancement to the EQ-5D-3L, it evaluates five key dimensions—mobility, self-care, usual activities, pain/discomfort, and anxiety/depression—using five response levels (1 = best health state, 5 = worst health state). It also includes a visual analog scale (VAS) from 0 to 100 for rating overall health status on the day of evaluation. Test-retest reliability ranges from 0.69 to 0.94 (ICC) ^63^, and it is widely employed in fibromyalgia and chronic pain studies for its capacity to provide an objective, comparative assessment of quality of life ^44,51,63–66^.

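### A target of 80 covers 20% attrition, not the stated 25%: losing a quarter of 80 leaves 60 completers, four below the 64 the protocol requires

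*Protocol*

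**What the plan says.** Section 4.4 (Sample size calculation) gives the whole calculation. The difference to detect is defined by "The between-group MCID is ≈14% of the FIQR total score". The other inputs are "Assuming SD=20, α=0.05 and power=80% with ANCOVA adjusted for baseline". From these it concludes "32 per group are required (total 64" participants), and it closes with "Allowing 25% attrition, the target sample size is 80".

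Three other sections bear on the check:
- Section 4.9 describes the FIQR as "yielding a total score from 0 to 100".
- Section 4.10 fixes the test: "Statistical significance will be set at two-sided p<0.05".
- Section 4.6 sets 1:1 allocation.

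The protocol gives no inflation formula, no other definition of attrition, no other target and no baseline-to-follow-up correlation.

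**The concern.** Attrition is a loss from those who enter the trial, so the allowance has to be checked by taking the loss from the target. A quarter of 80 is 20, which leaves 60. That is below the number the preceding sentence calls required. The figures 64, 25% and 80 therefore cannot all be right.

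The target matters because it decides when recruitment stops. If the assumed attrition occurs, the trial reaches its recruitment target and still misses its own evaluable number for the primary outcome. Section 6 commits the trial to CONSORT, so the calculation can be expected to appear in the report, where the mismatch is easy to see.

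**Working it through.** **Inputs**
- Required: 32 per group, 64 in total (section 4.4).
- Attrition 25%, target 80 (section 4.4).
- SD 20, α = 0.05, power 80% (section 4.4); two-sided (section 4.10); 1:1 allocation (section 4.6).
- Difference: 14 points. This is an assumption: it reads the 14% as a share of the 0–100 range in section 4.9, not of a baseline mean.
- Baseline correlation r: not stated. A range is shown below.

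**Step 1: reproduce 32 per group.** With the normal approximation, n = 2(1.960 + 0.842)² × 20² / 14² ≈ 32.04 per group. This matches the stated 32 after rounding down (rounding up gives 33). The stated number is thus what an unadjusted two-group comparison with SD 20 gives.

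**Step 2: reproduce 80.**
- N × (1 + d) = 64 × 1.25 = 80. This matches.
- N / (1 − d) = 64 / 0.75 = 85.3, so 86. This does not match.
- Per group: 32 / 0.75 = 42.7, so 43, or 86 in total. This does not match either.

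**Step 3: apply the loss to the target.**
- 80 × 0.75 = 60 (30 per group); 64 − 60 = 4 short.
- 1 − 64/80 = 0.20, so 80 covers a 20% loss.

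**Step 4: power with no gain from baseline adjustment** (standardised difference 14/20 = 0.7)

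| Method | 32 per group | 30 per group | Loss |
|---|---|---|---|
| Two-sample t-test | 78.7% | 76.0% | 2.7 points |
| Normal approximation | 80.0% | 77.4% | 2.6 points |

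**Step 5: power at 30 per group if ANCOVA reduces the SD.** Take 20 as the raw SD, so the residual SD is 20 × √(1 − r²).

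| Assumed r | Residual SD | Power (t-based) |
|---|---|---|
| 0.3 | 19.1 | 80% (79.8%) |
| 0.5 | 17.3 | 87% (86.8%) |
| 0.7 | 14.3 | 96% (96.2%) |

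On the t-based calculation, 80% power is kept at 30 per group from r of about 0.31.

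**The case against.** The strongest reply is that the planned analysis absorbs the shortfall. Section 4.4 refers to ANCOVA adjusted for baseline, section 4.10 plans that adjustment, and the 32 per group appears to take no credit for it. If 20 is the raw SD, a correlation of about 0.31 is enough to keep 80% power with 60 completers. This stands as an argument about power. It is why one cannot say outright that the trial falls below 80% at 25% attrition, although a reader might infer that. It does not make 80 an allowance for 25%. Nor can the plan rely on a margin it never states: section 4.4 gives no correlation and does not say whether 20 is a raw or a residual SD. If it is a residual SD, the adjustment is already counted and the loss in Step 4 applies.

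A reader might also set 76% beside the stated 80% and blame the attrition allowance for four points. That mixes a t-test figure with a nominal one. The t-test gives 78.7% even at the full 32 per group, so about 1.3 points come from the 32 itself and only about 2.7 from the missing four completers.

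Two other defences fail. Multiplying by 1.25 may be a familiar shortcut, but it does not protect the required number. The intention-to-treat commitment in section 4.10 does not help either: assessments are made only at t0 and t1 (section 5.3), so a participant lost before t1 has no post-intervention FIQR score.

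**Conclusion.** The attrition statement is wrong as written. At the attrition the protocol assumes, 60 participants (30 per group) remain instead of 64. Equivalently, the target is 6 below the 86 that a 25% loss would need. This follows from the protocol's own figures alone and needs no assumption about effect size or correlation.

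The power consequence is smaller and conditional. It is about 2.7 points, assuming a 14-point difference, SD 20 and no gain from baseline adjustment. With a moderate baseline correlation, 80% power is kept. The documents therefore support a shortfall in evaluable number, but not a firm claim that the trial is underpowered. The slip biases neither the treatment estimate nor the type I error. It should be fixed, because a stated design figure is incorrect and correcting it is easy.

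**What to change.** Keep the target of 80 and restate the allowance, for example: *The target of 80 participants allows for 20% attrition (64 completers, 32 per group); with 25% attrition, 60 completers (30 per group) would remain.* If a power figure is given for 60 completers, state the baseline correlation it assumes and whether the SD of 20 is raw or residual. State also that the 14% means 14 points on the 0–100 scale, if that is the intended reading.

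This costs one sentence and no extra participants. Only if a 25% loss must be fully covered does the target need to change, to 86 (43 per group), at a cost of six more participants.
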